## Abstract

**Background:**

Community mental healthcare has significantly grown since de-institutionalization. Despite progress, service fragmentation and gaps in service provision remain key barriers to effective community care in England. Recent mental healthcare policies highlighted the need to transform service provision by developing patient-centred, joined-up community mental healthcare. In response to policy guidance, a system-wide community mental healthcare model was developed in Peterborough (England). The “Peterborough Exemplar” is based on two main pillars: (1) the creation of knowledge exchange pathways to strengthen interorganizational relationships, and (2) the development of new, accessible community services addressing existing service gaps. This paper presents the protocol developed to evaluate the Peterborough Exemplar.

**Methods:**

A quasi-experimental design with an intervention group and a nonequivalent comparator group has been developed to compare service provision provided in Peterborough pre- and post-intervention with services provided in Fenland, a neighbouring area where service users access usual care. Two evaluation methods will be employed to compare service provision between the two groups: (1) outcome measures completed by service users and carers will be analysed to assess quality of life and service satisfaction, and (2) service activity data will be analysed to assess service usage. In addition, qualitative interviews will be conducted with staff members of participating organizations to explore the implementation of the Exemplar in Peterborough and evaluate knowledge exchange processes among local service providers. A matched control approach will be used to compare outcome measures between the two areas. Descriptive and inferential statistics, including chi-square tests, will be used to analyse service activity data and examine differences between the two areas. A thematic analysis will be adopted to analyse qualitative data.

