## The Peterborough Exemplar community mental healthcare model

The components of the Peterborough Exemplar were developed based on the needs of the local population. Local intelligence was used by the Exemplar partners to identify parts of the service system that are most challenged. Information sources used included (i) data on local deprivation, health and mental health prevalence and service utilization; (ii) consultation with key stakeholder groups across the system, including general practitioners (primary care), mental health professionals (secondary care), local third-sector organizations and social care; and (iii) service user and carer feedback. Two main areas of intervention were identified as an outcome of this exercise, which formed the main pillars of the Exemplar: (1) interorganizational relationships and (2) service development based on local demand.

The first pillar of the Peterborough Exemplar aimed to systemize knowledge exchange and improve relationships between local service providers. Specifically, the pillar introduced the following: routine clinical meetings between primary and secondary care, called “virtual clinics”; a liaison team offering advice and support across the system for community-based interventions; mental health professionals providing expertise to the primary care mental health service (PCMHS) for assessing patients with complex needs; and a website strengthening information dissemination by collating local mental health and well-being resources. The second pillar focused on developing new services with lower access thresholds, including services on psychological skills, PDs and peer support, services for individuals with a dual diagnosis, a team supporting engagement with social prescribing, a mental health pharmacist and a social care pathway operating at a primary care level. The peer support groups, dual diagnosis service, engagement with social prescribing and social care pathway are jointly organized and delivered by the mental health trust, third-sector organizations and social care, demonstrating the implementation of elements of integrated care. Additional file 1: Table S1 presents a description of each of the pillars and components of the Peterborough Exemplar.

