## Design

The composition of the Peterborough Exemplar was based on the following: (1) the creation of new services (e.g. new services for PDs and psychological needs), (2) the establishment of interorganizational processes (e.g. multi-agency meetings, liaison role of professionals) and (3) the involvement of multiple service providers. It can thus be defined as a complex intervention consisting of “interactive components” at intra- and interorganizational levels aimed at improving organizational performance and patient outcomes [23, p. 1, 24, 25].

Four main objectives were identified to assess the impact of the Peterborough Exemplar on mental health service provision and its implementation:(i)Evaluating service user and carer outcomes on quality of life and service satisfaction(ii)Examining service activity across the local health services system(iii)Assessing the economic impact of the Exemplar(iv)Exploring the implementation process of the Exemplar.

To address the evaluation objectives, a quasi-experimental design comparing service provision in two geographical areas and a qualitative method exploring Exemplar implementation have been employed. Specifically, the evaluation will adopt a quasi-experimental design by comparing an intervention group with a nonequivalent comparator group pre- and post-intervention [27]. Evaluations of complex interventions can follow both experimental and non-experimental designs depending on the structure of the intervention and the context within which it is implemented [23, 26]. Adoption of non-experimental designs is recommended when the implementation of an intervention is determined by policies, service demand or patient needs, rather than by researchers or when the implementation precedes the development of an evaluation [23, 26]. Quasi-experimental designs are observational designs appropriate for assessing “real-world effectiveness” and where health service use is based on clinical decision and patient choice, rather than on researcher’s decision via randomization [27, p. 39]. Using qualitative methods can provide valuable insights into the processes of implementation and can contribute to identifying elements about a complex intervention that may not have been initially considered [24].

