## Study setting

### Description of geographical areas

The study will compare service provision in two geographical areas. Services provided in Peterborough where the Exemplar is implemented are defined as the intervention group and will be compared with local services in Fenland, which was selected as the nonequivalent comparator group. Fenland is a neighbouring area where service users access usual care. Peterborough and Fenland areas are part of the Cambridgeshire and Peterborough County located in the East of England (United Kingdom). The nonequivalent group (Fenland) was selected among the six areas of the county as the most suitable area to be compared with Peterborough based on similarities in the populations between the two areas and service provision, allowing assessment of whether the intervention impacted the area where it was implemented [30].

Out of the 62 most relatively deprived lower-layer super output areas (LSOAs) (i.e. small population area) existing in Cambridgeshire and Peterborough County, 46 LSOAs are in Peterborough, and 11 LSOAs are in Fenland [31]. A multimorbidity analysis conducted by local authorities showed that both Peterborough and Fenland present a statistically significantly higher rate of physical and mental health comorbidity (8.5.% and 10.0%, respectively) compared to the county’s average (7.5%), and a statistically significantly higher rate in the prevalence of two or more morbidities in adults (25–84 years old) in comparison with the county’s average [32]. The two areas, together with the area of Huntingdon (located in the west of the county), present statistically significantly higher prevalence rates for health conditions including stroke and hypertension, coronary and heart disease, along with higher rates for dementia, depression and learning disabilities compared to the county’s average [33]. The total population of the Peterborough area is 184 000 residents, and Fenland has 95 000 residents, as recorded in the 2011 Census [34, 35]. Population differences will be taken into consideration in the analysis stage. Fenland is a rural area, while Peterborough is partially rural; thus, differences in geographical characteristics may affect access to services. However, service provision has also been offered online since the beginning of the COVID-19 pandemic, and online offers will likely continue to be available.

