### Local mental health service provision

Mental health services across the county are provided by one NHS mental health trust (the Cambridgeshire and Peterborough NHS Foundation Trust). Social care and third-sector organizations also offer services that support mental health. Third-sector organizations may be local charities or local branches of national or regional charities. Primary care is provided by general practices (GPs) operating in each geographical area. Primary care has recently been organized in coalitions, called primary care networks (PCNs), that enable coordination of care.

To evaluate the impact of the Peterborough Exemplar across the local area, multiple levels of care were considered. The study design includes services introduced or redesigned by the Peterborough Exemplar, such as the PCMHS and the psychological skills services (PSS), as well as existing services that may be impacted as an outcome of the Exemplar implementation, for example the Trust’s mental health adult specialist services. Fenland services included in the study design were selected by identifying corresponding services between the two areas. Table 1 presents the services that will be included in the evaluation.

**Table 1 Tab1:** Services included in the evaluation of the Peterborough Exemplar

Level of care	Service	Intervention (Peterborough)	Nonequivalent comparator (Fenland)
Primary care—physical health	General practitioners	✓	✓
Primary care—mental health	Primary care mental health service	✓	✓
Primary care—mental health	Psychological skills services Personality disorders community service Dual diagnosis service Social care pathway	✓	–
Secondary care—mental health	Adult specialist services providing mental healthcare	✓	✓
Social care	Social care pathway for specialized needs	✓	✓
Third sector	Third-sector organizations	✓	✓

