Qualitative semi-structured interviews (3) will be conducted to explore the implementation process of the Exemplar in Peterborough. Collection and analysis of qualitative data will be conducted throughout the 18-month evaluation period (see Additional file 2). Following the analysis of qualitative and quantitative data, a data triangulation plan will be generated, allowing assessment of the intervention using multiple data sources [36]. The selection of evaluation methods was also informed by exemplar programming theory, which outlined the target outcomes of the Peterborough Exemplar. The next sections detail each evaluation method.Evaluation of service user and carer outcomesRoutinely collected outcomes measures completed by service users accessing the Exemplar services and the secondary care specialist teams will be analysed pre- and post-treatment. Quality of life and care satisfaction of service users will be assessed using the DIALOG tool, an 11-item measure combining eight questions on satisfaction with quality of life and three on satisfaction with service provision [37]. A brief questionnaire with four further questions on service satisfaction and the impact of the COVID-19 pandemic is also included, as the Exemplar implementation began during the pandemic period. The EuroQol EQ-5D-5L will also measure quality of life, for use in the economic analysis of the Exemplar [38]. Finally, a brief carer-rated service satisfaction measure will be included in the evaluation to assess carers’ satisfaction with services. The carer measure has been developed within the Trust in collaboration with carers and is used to routinely evaluate carer satisfaction with provided care.Local intelligence used by the Exemplar partners to identify investment priorities highlighted service demand for PDs in particular. To assess the impact of the personality disorders community service (PDCS), the Standardized Assessment of Severity of Personality Disorder (SASPD) measure [39] will be included in the evaluation. The SASPD is completed by service users at the PDCS pre-treatment and post-treatment in both the intervention and comparator groups. The SASPD measure will be used to assess the severity level of the PDs of service users accessing the new Exemplar PD services (intervention group) and compared with the severity level of those accessing PD services in Fenland (comparator group).Measures included in the evaluation are part of clinical routine practice in both the intervention and comparator groups. A matched control approach will be adopted to compare outcomes measures between the intervention and comparator groups. In this approach, study participants between the two groups are matched based on key covariates by using, for instance, nearest-neighbour matching or weighting techniques [40]. When randomization is not possible (e.g. in a quasi-experimental design), a matched control approach allows for control of external factors that can affect the relation between an intervention and its outcome and strengthens internal validity [40, 50]. Matching between intervention and comparator groups will be based on independent variables, including age, gender, employment, ethnicity and service provided.Descriptive statistics will also be used to describe baseline characteristics of service users in the two areas. Missing responses in outcomes measures will be managed based on analytical frameworks of the selected measures (i.e. DIALOG, EQ-5D-5L and SASPD). A detailed statistical analysis plan is currently being developed to demonstrate the rationale and steps of the matched control analysis.Evaluation of service activityService activity will be analysed to assess service usage and examine differences between the intervention and comparator groups pre- and post-intervention. Specifically, routinely collected service activity data of service users who had at least one contact in a team within the Adult Specialist Directorate of the Mental Health Trust will be analysed for both geographical areas over the 18-month evaluation period. Service activity data will include demographic variables (e.g. age, gender) and service activity variables (e.g. referral source, dates of appointments, treatment team and discharge reason). Service activity data from other geographical areas or from other Trust directorates will be excluded. Aggregated data on service activity will also be obtained from Exemplar partners (social care, third-sector and primary care services). Those will include the following: (i) primary care—the number of patients seen by GPs and percentage of patients visiting the GP with a mental health need; (ii) social care—the number of new contacts and percentage of new enquiries for people with primary support reason mental health; and (iii) third sector—attendance in the peer support groups for PDs. Aggregated data will increase our understanding of service demand in the intervention and comparator groups. All quantitative data will be saved in electronic folders of the password-protected virtual work environments of the lead author and the economist researcher.Descriptive statistics will be used to present the characteristics of the patient cohort contained in service activity datasets, including percentages of demographic characteristics, services accessed by patients and diagnosis and to assess completeness of data. Changes in trends in key service utilization indicators during the 18-month evaluation period (*T*0–*T*4) between the two study groups will be analysed using *χ*^2^ (chi-square) tests. Service activity indicators include referral sources, number of contacts and access to specialist services in secondary care. Stata software (version 16) will be used to conduct the statistical analysis [41]. A detailed statistics and health economic analysis plan is currently being developed that outlines the statistical analysis of service usage.Taking into consideration data collection and analysis requirements of the selected methods and the resources available to the evaluation, assessing the Exemplar’s impact on service users focused on quantitative methods only (routine outcome measures and service activity usage). Quantitative methods allow data collection from a larger cohort of service users, are routinely collected within the Mental Health Trust and are less time-consuming for service users. However, qualitative methods, such as semi-structured interviews, can offer in-depth understanding of service users’ experience with service provision and complement quantitative findings in assessing the impact of complex interventions [24]. Collection of qualitative data from service users will be explored if the evaluation funding is extended.Evaluation of the implementation processQualitative interviewing will be used to explore individuals’ perspectives around a studied phenomenon by having an in-depth conversation [42]. Qualitative data collection will focus on three main themes: (i) the implementation of the Exemplar in Peterborough, (ii) the relationships among local service providers and (iii) the role of the patient-centred approach in the Exemplar. Semi-structured interviews are often accompanied by an interview guide to assist with focusing the discussion on selected topics [43]. Thus, an interview guide has been developed based on the three main themes of interest (see Additional file 3). Selection of interview questions was also informed by suggestions from the PPI group, professionals and the steering group coordinating the Peterborough Exemplar implementation.Purposive sampling will be used to select interview participants based on their relevance and richness of knowledge around the interview guide topics [44]. Staff members from service providers and funders participating in the implementation of the Peterborough Exemplar will be invited for an interview. Potential participants from four organizational levels will be invited: (i) frontline workers from primary care, social care and the third sector, (ii) frontline workers from secondary care, and (iii) managers and (iv) senior management staff from Exemplar stakeholder organizations. Each level includes professionals from different teams of the same organization or different organizations participating in the delivery of the Peterborough Exemplar. Interviewing key stakeholders across professional levels will allow the collection of rich and diverse information about the implementation process of the Exemplar.Focus groups could also be employed to explore professionals’ perspectives discussed in a group environment [45]. In this study, qualitative interviewing was preferred in order to reduce potential hesitancy among participants in expressing sensitive or critical views [45] in the presence of colleagues, for instance on topics about the collaboration among teams or improvements needed in the Exemplar implementation. A limitation of qualitative interviewing, however, is that topics generated from a shared understanding of participants—as can ideally happen within a focus group—may be lost [46, 47].Potential participants will be identified with the help of a gatekeeper from each Exemplar partner. A gatekeeper will indicate staff members who work in a service or team participating in the Exemplar (e.g. PDCS or PCMHS) or staff members whose work may be impacted by the Exemplar (e.g. GPs). Staff members whose work is not related to or impacted by the implementation of the Peterborough Exemplar will be excluded. Potential participants will receive an email invitation with a participant information sheet and a consent form developed by the lead author. One reminder will be sent to potential participants 2 weeks following the initial invitation. Participation in interviews will be anonymous and confidential. All interviews will be conducted via Microsoft Teams, and interviews will be recorded with an audio recorder. It is estimated that each interview will last between 45 and 60 minutes. Anonymized recordings will be transcribed verbatim, and recordings will be deleted following transcription completion.A thematic analysis will be conducted to analyse interview transcripts, a method frequently used to analyse qualitative data [48]. Thematic analysis is a method used to query a textual dataset with the aim of finding reoccurring meanings that capture topics related to the studied subject, also called “themes” [48, p. 79]. Data collection and thematic analysis will be conducted by the lead author, who has 3 years of experience on qualitative data collection and analysis, including thematic analysis. Four samples of anonymized transcripts will be discussed with GJ, KF and JP to review the coding process. GJ has received training on analysis qualitative data, and KF and JP have experience in conducting qualitative research in healthcare settings. GJ and JP’s clinical experience will also inform data analysis and interpretation. NVivo data analysis software will be used to assist with analysis of interview transcripts [49].

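### The chi-square tests named for service activity ignore the grouping of users in teams and practices, so their p-values may be too small, and one area per arm rules out a confirmatory reading

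*Protocol article*

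**What the plan says.** **Exposure.** It is defined by place, with one area on each side. Under Description of geographical areas: "Services provided in Peterborough where the Exemplar is implemented are defined as the intervention group", and "Fenland is a neighbouring area where service users access usual care". The Design section describes the study as "comparing an intervention group with a nonequivalent comparator group pre- and post-intervention".

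**Delivery.** The Exemplar works partly through organisations. The section on the Exemplar model lists "routine clinical meetings between primary and secondary care, called “virtual clinics”; a liaison team offering advice and support across the system", among other components.

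**Grouping of users.** Under Local mental health service provision: "Primary care is provided by general practices (GPs) operating in each geographical area". The individual activity records, described in the service activity part of Methods, belong to "service users who had at least one contact in a team within the Adult Specialist Directorate of the Mental Health Trust". Treatment team is given there as an example of the variables held.

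**Test.** The abstract states: "Descriptive and inferential statistics, including chi-square tests, will be used to analyse service activity data and examine differences between the two areas". The service activity part of Methods is firmer. It says, with no qualifier, that chi-square tests will be used to analyse how trends in the main usage indicators change between the two groups over the 18 months. The indicators are referral sources, number of contacts and access to secondary-care specialist services. The same part of Methods says that a fuller statistical and health economic plan for service usage is being written.

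The article does not mention clustering by practice, team or area. The Discussion admits that such designs cannot control every factor, but it does not raise this point.

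**The concern.** An ordinary chi-square test draws its error from independent observations. Users of one team share staff and thresholds, and users of one practice share referral habits. Two of the three named indicators, referral source and access to specialist services, are plausibly shaped by those shared features. If so, users in one cluster resemble each other, the effective sample is smaller than the head count, and the test rejects too often when nothing has changed.

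A second layer sits above this. With one area per arm, no user-level p-value contains any variation between areas.

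Data are to be analysed at the end of each period to guide delivery, and findings go to commissioners, Exemplar partners and NHS England. Overstated significance could therefore influence decisions both during and after the evaluation.

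**Working it through.** The article gives no sample size, significance level, ICC, number of teams or practices, or users per cluster. There is no figure of its own to reproduce, and what follows is an illustration on assumed inputs.

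**Step 1. Formulas.** For *m* users per cluster, each cluster lying wholly within one area (an assumption; the article does not say whether any team serves both areas):

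- design effect DE = 1 + (*m* − 1) × ICC
- true two-sided error of a nominal 5% independence test = 2 × [1 − Φ(1.96 / √DE)]

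**Step 2. Worked cases.**

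- ICC 0.005, *m* = 20: DE = 1 + 19 × 0.005 = 1.095; 1.96/√1.095 = 1.87; error 6.1%.
- ICC 0.01, *m* = 50: DE = 1 + 49 × 0.01 = 1.49; 1.96/√1.49 = 1.61; error 10.8%.
- ICC 0.02, *m* = 100: DE = 1 + 99 × 0.02 = 2.98; 1.96/√2.98 = 1.14; error 25.6%.
- ICC 0.05, *m* = 200: DE = 1 + 199 × 0.05 = 10.95; 1.96/√10.95 = 0.59; error 55.4%.

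**Step 3. Full assumed grid: true error of a nominal 5% test.**

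| ICC | *m* = 20 | *m* = 50 | *m* = 100 | *m* = 200 |
|---|---|---|---|---|
| 0.005 | 6.1% | 7.9% | 10.9% | 16.5% |
| 0.01 | 7.2% | 10.8% | 16.5% | 25.7% |
| 0.02 | 9.5% | 16.4% | 25.6% | 38.0% |
| 0.05 | 16.0% | 29.1% | 42.2% | 55.4% |

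The correct standard error is √DE times the one the test uses, which is 1.05 to 3.31 times over this grid.

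**Step 4. Check by simulation.** 10,000 runs per scenario used beta-binomial clusters, a true proportion of 0.30 in both areas and no Exemplar effect. Clusters numbered 10 against 5 or 20 against 10, with ICC 0.01, 0.02 or 0.05 and *m* = 50 or 100. The ordinary chi-square test rejected in 10.6% to 41.8% of runs, in line with the formula. A t-test on cluster proportions rejected in 4.5% to 5.3%.

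**Step 5. Area level.** Assume 1000 against 500 users, a proportion of 0.30, and independent true area proportions with standard deviation *s*. The sampling variance is 0.30 × 0.70 × (1/1000 + 1/500) = 0.00063. The true variance of the difference is 0.00063 + 2*s*². The error is then 8.8%, 19.3% or 31.8% for *s* of 1, 2 or 3 percentage points. Clustering on team or practice does not repair this, because two areas give no estimate of *s*.

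Steps 2 to 5 describe a single cross-sectional comparison. In a contrast of pre/post change, the part of the cluster or area difference that stays constant cancels, and only variation in the change remains.

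**The case against.** **The detail may sit in a plan not shown.** Variance estimation is ordinary analysis-plan content, a service-usage plan is announced, and the abstract's wording does not exclude other methods. This stands in part: a cluster-aware analysis is not ruled out. But the article is not merely silent. Methods names a specific test without qualification, and that test's independence assumption does not fit the design. A plan that corrected it would have to depart from the published method.

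**The design is pre/post.** Stable team or practice differences could largely cancel in a true contrast of change, so the error rates above may be too high for such an analysis. This stands. It is also why a reader who infers that ordinary practice differences will be reported as Exemplar effects goes further than the article allows. A plain chi-square on pooled counts does not, however, deliver that contrast by itself.

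**The size is assumed.** This stands. At small ICC and small clusters the error is close to nominal, so error well above 5% cannot be stated unconditionally. Nor does the article mention confidence intervals, so the point concerns standard errors and p-values.

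**The outcome measures.** A reader might infer the same fault for DIALOG, EQ-5D-5L and SASPD from "A matched control approach will be adopted to compare outcomes measures between the intervention and comparator groups". The document does not support that. Matching users does not fix how variance is estimated, service provided is itself a matching variable, and the steps are left to a separate analysis plan.

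**Limits are already admitted.** The comparator is called nonequivalent, and the Discussion concedes uncontrolled factors. That covers bias in general terms. It does not tell readers that the p-values omit between-cluster and between-area variation.

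**Conclusion.** The point holds for service activity. The named chi-square tests assume independent observations, while exposure is by area and users are grouped in teams and practices. With positive within-cluster correlation the p-values are too small. For a single-period comparison, the true error of a nominal 5% test lies between about 6% and 55% over an ICC of 0.005 to 0.05 and 20 to 200 users per cluster. Both inputs are assumptions, and a genuine contrast of change would lower the figure by an amount that the article does not allow one to estimate.

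Separately, and whatever the ICC, one area per arm means that no standard-error correction can distinguish the Exemplar from other differences between Peterborough and Fenland.

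No error is established in the matched outcome comparison. This should be changed while the service-usage plan is still being written.

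**What to change.** 1. Replace the plain chi-square for service activity with a cluster-aware contrast of pre/post change between the areas. One form is a regression suited to each indicator, with an area-by-period term and small-sample-corrected errors clustered on treatment team.
2. Where the indicator is itself access to a specialist team, the team reached is close to being the outcome. Clustering on referring practice is preferable there, if a practice code can be added to the extract.
3. State, in the plan and with the results, that with one area per arm the p-values exclude area-to-area variation and are not confirmatory tests of the Exemplar. This statement is essential, because items 1 and 2 address only variation within an area.
4. When the analysis plan for the matched comparison is completed, say there how its variance allows for teams or practices. This is a request, not a correction.

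**Cost.** Treatment team is already listed among the activity variables, and Stata, the stated software, supports cluster-robust analysis, so items 1 and 3 need only code and text. A practice code is a further field, and the article does not show whether it is available. The p-values will be less favourable. Clusters may also be few, since the article gives no number of teams or practices; that is why the small-sample correction is needed, and precision may be poor.
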